## 4. STUDY POPULATION

### 4.1 Population (base)

Patients will be included at the outpatients clinic of the urology department of the participating centres. There are several possible causes why patients have to self-catheterize. As described above, urinary retention or post void residue can be caused by urinary tract dysfunction due to idiopathic or neurogenic urinary retention. All included patients are able to self-catheterize and are experienced for at least two weeks.

### 4.2 Inclusion criteria

In order to be eligible to participate in this study, a subject must meet all of the following criteria:

- Male/Female patients  $\geq 16$  years old
- Diagnosed with urinary retention or significant post-void residue due to non-neurogenic or neurogenic causes
- Expected chronic, but at least for a duration of twelve months, necessity for daily drainage of the urinary bladder
- Be able to administer self CIC via the urethra daily and have at least two weeks of experience in CIC.

### 4.3 Exclusion criteria

A potential subject who meets any of the following criteria will be excluded from participation in this study:

- Age  $< 16$  years
- Temporary use of catheterization because of transient causes
- Known significant urethral stricture which prevents CIC
- Urinary tract stones
- Bladder augmentation
- Non-urethral catheterization
- History of bladder cancer with active follow-up
- The use of immunosuppressives for transplantation or auto-immune diseases
- Neurocognitive disease which prevents complete comprehension of the study

### 4.4 Sample size calculation

The number of studies that have investigated the effects of single use and disposable catheters is limited. Our initial sample size calculation was based on data from a Cochrane review by Prieto et al. (2015), which was later found to contain inaccuracies in

data selection and extraction (9). Specifically, six of the eight trials included in the review did not contain consistent or accurate data compared to their originally published versions. Unfortunately, these erroneous data were used as the basis for our initial sample size calculation ( $n=456$ ). We were therefore required to perform a new sample size calculation based on the revised 2021 Cochrane review with corrected data (14). The revised Cochrane review included ten studies comparing single-use catheters to reusable catheters. To prevent confounding effects related to insertion techniques (clean vs. sterile), six of these studies employed the same insertions method in both study arms. Among these, three studies provided usable data regarding the number of sUTI events in each group. For single use 18 events out of 68 were observed, for reusable 20 events out of 69. This leads to the proportions of 0.26 and 0.29. Further we applied a power of 0.80 and a one-sided alpha of 0.025 (it is customary to adjust one-sided alphas to the half of 0.05). In our previous calculation, the non-inferiority margin had been determined based on 50% of the mean proportions, following the recommendation of Althunian et al. (15) However, with the corrected data, this would have resulted in an increase in the non-inferiority margin to 14%. As this was deemed inappropriate, we opted to maintain the margin at 11%. The sample size is then calculated with:  $n = ((Z(1-\alpha) + Z(1-\beta))^2 [ps(1-ps) + pe(1-pe)]) / ((ps-pe-d)^2)$ , the formula developed by Blackwelder et al in 1982 (16), leading to 154 effective cases in each group. Anticipating a dropout of 20% (17), this must be divided by 80% and rounded upwards. This results in 2 times 193 participants, a total of 386.

Because the lack of comparable non-inferiority designed trials with the same primary outcome measurement (sUTI) it is chosen to look at non-inferiority trials with a primary outcome measurement of (treatment of) sUTI. All these trials handled a non-inferiority margin of 10% (18) (19-22), and two trials even 15% (23, 24). The head researchers and clinicians of the departments of urology and medical microbiology agreed on the 11% margin to be clinical acceptable.

In addition, we encountered the unique challenge of conducting a study with a significantly extended follow-up period of one year, in contrast to the previous studies used in the sample size calculation above, with a shorter follow-up of 2-4 months. Recognizing the impact of time on the occurrence of urinary tract infections (UTIs) and the need to account for this extended observation period, we also performed a sample size calculation that considered the monthly UTI rates observed by Vapnek et al. (25) This calculation factored in not only the proportion of UTIs but also the temporal aspect, recognizing that the incidence of UTIs may vary over time. Vapnek et al. found that single-use catheters had

an average of 0.13 UTIs per month (SD 0.18) and multiple-use catheters had an average of 0.14 UTIs per month (SD 0.21) per patient (25). We applied the same power of 0.80 and an one-sided alpha of 0.025. A non-inferiority margin of 7% has been determined based on 50% of the means following the recommendation of Althunian et al. (15) We used the most conservative standard deviation of 0.21 and the sample size calculation was performed using the formula developed by Julious:  $n = f(\alpha, \beta) \times 2 \times \sigma^2 / d^2$  (26). This calculation led to a requirement of 152 effective cases in each group. Anticipating a dropout rate of 20%, this figure was divided by 0.80, resulting in a total sample size of 382 participants (191 in each group). Since the sample size of 382 is almost equal to our sample size that does not correct for time (n=386), we will include 386 participants to account for both methods.

Sample size: 386 patients.

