| Week 0, baseline | Clinical visit 1         | 
 
- Inclusion of patients
 
- Informed consent signing
 
- Randomization into two groups:
Intervention group (reusable) N = 228
Or
Control group (single use) N = 228
 
- If randomized in intervention group, schooling on how to use the reusable catheter is provided by the continence nurse
 
- Urinary sample will be obtained for testing
 
 | 
 
- EQ-5D-5L
 
- SF-Qualiveen
 
- ISC-Q
 
- IncasaQ
 
- Two opinion questions about the environmental and financial burden of catheters
 
 |
| Week 1           | Telephone call           | Evaluation of catheter use, patients will be asked for adverse events and possible risen questions will be answered.                                                                                                                                                                                                                                                                                                                                   |                                                                                                                                                                                                                     |
| Week 6           | Telephone call           | To evaluate the first impression, evaluate if the cleaning routine of the catheter is correctly preformed, asked for adverse events through standardized questions in Gemstracker/LimeSurvey and possible risen questions will be answered.                                                                                                                                                                                                            | 
 
- EQ-5D-5L
 
- SF-Qualiveen
 
- ISC-Q
 
- IncasaQ
 
- iMCQ
 
- iPCQ
 
- PGI-I
 
                                           |

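### 154 evaluable patients per arm does not give 80% power for the 11% margin on the UTI proportion, so the total of 386 is supported by the monthly-rate calculation alone

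*Combined protocol and SAP*

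**What the plan says.** Protocol 4.4 and SAP 6.3 carry the same two calculations.

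The first is on the proportion of patients with a symptomatic UTI. Its source data are three studies from a revised systematic review: "For single use 18 events out of 68 were observed, for reusable 20 events out of 69". The text rounds these to 0.26 for single use and 0.29 for reusable catheters. Next: "Further we applied a power of 0.80 and a one-sided alpha of 0.025". Half of the mean proportion would have given a 14% margin, and the text comments: "As this was deemed inappropriate, we opted to maintain the margin at 11" (per cent). A Blackwelder formula with denominator (ps-pe-d)^2 is printed, "leading to 154 effective cases in each group". Dividing by 0.80 for dropout gives 193 per arm, 386 in total.

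The second is on UTIs per patient-month. It takes from a cited randomised catheter trial "an average of 0.13 UTIs per month (SD 0.18) and multiple-use catheters had an average of 0.14 UTIs per month (SD 0.21) per patient", a 7% margin and SD 0.21. It states 152 per arm, and 382 in total after dropout.

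The two totals are then joined: "we will include 386 participants to account for both methods".

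In the SAP, the hypotheses (3.3.1), decision rule (3.3.3) and primary analysis (6.1.2) all use the monthly rate with the 7% margin. UTI during follow-up as a yes/no outcome is listed as secondary. The schedule in Protocol section 3 still shows "Intervention group (reusable) N = 228", and the same number for the control group.

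**The concern.** A UTI is an unfavourable event and the plan expects slightly more of them with reusable catheters. In a non-inferiority calculation an expected disadvantage uses up part of the margin: 11 points less 3 leaves 8. The printed denominator, filled with the stated values, gives 14 points, which happens to equal the margin that the same paragraph turns down. Sample size varies with the inverse square of this distance, so the effect is large.

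At stake is the stated power for the proportion. The 11% margin is the only one that the text says the clinicians agreed was acceptable, and Protocol 10.1 still plans chi-square tests for binomial outcomes. A reader could set the yes/no UTI result against 11% and believe that the trial was sized for that comparison. The closeness of 382 and 386 also reads as two methods confirming each other.

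**Working it through.** **Inputs** (Protocol 4.4): ps = 0.26, pe = 0.29, d = 0.11, one-sided alpha 0.025, power 0.80, dropout 20%. The multiplier is (1.960 + 0.842)^2 = 7.849. The variances are 0.26 × 0.74 = 0.1924 and 0.29 × 0.71 = 0.2059, with sum 0.3983.

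**Reproducing 154**
- Formula as printed, stated inputs: denominator (0.26 - 0.29 - 0.11)^2 = 0.14^2 = 0.0196, so n = 7.849 × 0.3983 / 0.0196 = 159.5, i.e. 160, not 154.
- 0.26 in both variance terms, distance 0.14: 7.849 × 0.3848 / 0.0196 = 154.1. This matches the stated 154, and 154 / 0.80 = 192.5, i.e. 193.
- Keeping both variances, 154 would need a distance of sqrt(7.849 × 0.3983 / 154) = 0.1425.

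Each route to 154 uses a distance of about 14 points.

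**Requirement with an 11% margin**
- 0.26 v 0.29, distance 0.11 - 0.03 = 0.08: 7.849 × 0.3983 / 0.0064 = 488.5, i.e. 489 per arm (612 after dropout, 1,224 in total).
- Unrounded 18/68 = 0.2647 and 20/69 = 0.2899, difference 0.0251: 436.6, i.e. 437 per arm (547 after dropout, 1,094 in total).
- No true difference, 0.26 in both arms: 7.849 × 0.3848 / 0.0121 = 249.6, i.e. 250 per arm (313 after dropout, 626 in total).

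The printed formula is sound if ps and pe are UTI-free proportions: (0.74 - 0.71 - 0.11)^2 = 0.08^2, again 489.

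**Power at 154 per arm, 11% margin**
- 0.26 v 0.29: Phi(0.08 / sqrt(0.3983/154) - 1.96) = 34.9%. The Farrington-Manning method and a simulation both give 35.1%.
- Unrounded proportions: 38%.
- No true difference at 0.26: Phi(0.11 / sqrt(0.3848/154) - 1.96) = 59.5%, about 60%.
- All 193 per arm with no dropout: 42% (rounded) or 46% (unrounded), and 69% with no true difference.

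**The rate calculation**
- n = 7.849 × 2 × 0.21^2 / margin^2. The stated margin 0.07 gives 141.3, i.e. 142. Half the mean of 0.13 and 0.14 is 0.0675, which gives 151.9, i.e. the stated 152. Both take a true difference of zero.
- Power is Phi((margin - difference) / (0.21 × sqrt(2/154)) - 1.96), with standard error 0.0239 at 154 per arm:

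| Margin | Zero difference | 0.14 v 0.13 |
|---|---|---|
| 0.07 | 83% | 71% |
| 0.0675 | 81% | 67% |

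- With the cited SDs of 0.18 and 0.21 in place of 0.21 in both arms, power at 0.14 v 0.13 and margin 0.07 is 77%.

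**The case against.** The strongest reply is that the trial's conclusion does not depend on the faulty calculation. The SAP contains no test of the UTI proportion against 11%. That margin appears only in the sample-size text, and the yes/no outcome is secondary with no non-inferiority rule. The rate calculation by itself asks for 382, so 386 would stand if the first calculation were deleted. All of this stands, and it limits the consequence to what the documents claim about power.

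A second reply is that zero true difference is a common planning assumption in non-inferiority trials, and the rate calculation uses it. That is fair. It moves the power for the proportion from 35% to about 60%, still well short of 80%.

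A third is that 154 is a pessimistic number for the rate endpoint. SAP 6.1.2 divides total UTIs by total follow-up time, and the intention-to-treat set keeps patients who started but did not complete, so dropouts contribute time until they leave. SD 0.21 is also the larger of the two cited. With all 193 per arm and margin 0.07, power at 0.14 v 0.13 is 80% (SD 0.21) or 85% (cited SDs). This stands as an upper bound, but the plan's own effective number after dropout is 154, and neither document says that the calculation assumes zero difference.

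**Conclusion.** The stated 80% power for an 11% margin on the UTI proportion is wrong as written in both documents, and so is the statement that 386 covers both methods. At 154 per arm, power is about 35-38% if the planning proportions hold and about 60% if the arms are equal. This rests on the plan's own proportions, alpha and margin and on the normal approximation. The 0.03 disadvantage itself comes from only 137 patients (68 + 69), so the range is a better summary than its lower end.

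The confirmatory rate test and its decision rule are unaffected. The point should be fixed, but it does not put the trial's primary analysis in doubt.

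A reader might infer more in three ways, and the documents do not support these readings:
- That a sign error is proven. The printed formula with the stated inputs is the sign-error route, but it gives 160. The exact match to 154 is the rejected 14% margin with 0.26 in both arms. The text cannot separate the two.
- That the rate endpoint has 80% power only if the arms are exactly equal. At 154 per arm, SD 0.21 and margin 0.07, 80% holds for a true difference up to about 0.003 per month (0.07 - 2.802 × 0.0239).
- That a definite power can be given for the 12-month proportion, since the planning proportions come from studies of 2-4 months. The documents do not say how the SD of the monthly rate divides into variation between and within patients, so any such figure rests on modelling that they do not supply.

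**What to change.** In Protocol 4.4 and SAP 6.3:
- Remove the 154-per-arm calculation as support for 386, or keep it with its true power, and delete the clause saying that 386 serves both methods.
- State that 386 rests on the monthly-rate endpoint, that its calculation assumes zero true difference, and what its power is at zero difference and at 0.14 v 0.13. State whether 0.07 or 0.0675 was used to obtain 152.
- State that the comparison of UTI proportions has about 35-60% power for an 11% margin at 154 per arm and is descriptive.

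As a separate clerical correction, change 228 per arm in the Protocol section 3 schedule to 193. The 228 is half of the superseded total of 456.

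The cost is a wording amendment to both documents and a less favourable power statement. No patients are added, and the primary outcome, margin and decision rule stay as they are.

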## 5. TREATMENT OF SUBJECTS

### 5.1 Investigational product

The reusable catheter that will be used in this trial will be obtained via Create Medic (<http://www.createmedic.co.jp/english/>), a Japanese medical manufacturer with broad experience on urological products. The reusable Cliny catheter ([http://www.createmedic.co.jp/files/topics/412\\_ext\\_11\\_0.pdf](http://www.createmedic.co.jp/files/topics/412_ext_11_0.pdf)) made by this CE-certified manufacturer, is widely used in Australia and has been shown to be safe. Because the catheter manufacturer is CE-certificated and the reusable catheter is considered to be a Class I healthcare device, it does not need a separate CE certificate from a notified body. The reusable catheter is registered in the Z-index and will be covered by the health insurances in the Netherlands. The reusable catheter can be introduced without lubricant because of a high quality smooth surface and will be stored in a holder containing Milton solution, a sterilizing fluid produced by Procter and Gamble which will be renewed every 24 hours. In this trial, the reusable catheters will be used for a period of two weeks, according to the manual of the Royal Children's Hospital Melbourne (<https://bit.ly/2tSsj9B>). Patients will be trained in using these catheters by continence nurses and will be provided a clear instruction on how to clean and store the catheters.

The control group will be using the single use catheters. These catheters used for intermittent catheterization, are disposable and already reimbursed by standard health insurance in the Netherlands. The choice of the single use catheter will be determined by the preference of the patient.

### 5.2 Use of co-intervention

Not applicable

### 5.3 Escape medication

Not applicable

## 6. INVESTIGATIONAL PRODUCT

### 6.1 Name and description of investigational product

The Cliny catheter is a catheter that is developed for reuse. The manufacturer, Create Medic, states that the catheter can be safely used for 30 days. In this trial a time period of two weeks for reuse is chosen, according to a manual of the Royal Children's Hospital in Melbourne.

### 6.2 Summary of findings from non-clinical studies

One non-clinical study is performed by Chan et al, who set up a trial to determine the efficacy of catheter sanitizing and storage for reuse. First catheters were inoculated with e. coli and after washed with antibacterial soap and microwaved or packaged and stored for period of 1, 3 and 7 days. Overall 44% of the catheters washed yielded e. coli vs 26% of the combined washed and microwave treatment, concluding that this is not an absolute way to sanitize catheters for intermittent catheterization (27).

### 6.3 Summary of findings from clinical studies

There is no literature available for the specific catheter used in this trial, but only of reuse of catheters in general.

A recent systematic review of Prieto et al on intermittent catheterization discussed the scarce evidence in the literature for the differences in safety and efficacy between single-use versus reusable catheters (9). This review concludes that the available data on CIC does not provide convincing evidence that single-use or reuse of catheters is a better strategy. The available trials evaluated were methodologically weak, were generally underpowered, outcome variables differed and follow up differed from up to 24 hours to 12 months. This reflects lack of reliable evidence, rather than evidence of no difference. This Cochrane review was forced to withdrawn in august 2017 with the argument that more fundamental research was necessary to obtain high level evidence (10). This opposing article (10) did an independent appraisal of the data and analyses present in the Cochrane review. In contrast to Prieto et al (9), their analyses revealed a trend to favour single over reusable catheters in respect to the main outcome of UTI.

Kovindha et al describe their cross sectional study on spinal cord injured men in Thailand who had uses CIC with an reusable catheter for over a year. An average time of reuse for each catheter was three years. After two years of reuse, electroscopic findings were encrustation of the catheter, but no obstruction in the lumens and 20% increase in

stiffness. They concluded that reuse of a silicone self-catheter is safe and acceptable for SCI men in development countries, due to low cost and ease of use. To reduce infections induced by catheterization, a shorter period of reuse is recommended and cleansing and disinfection of the catheter should be properly done (8).

Getliff et al performed an earlier systematic review in 2007 and summarizes the evidence on the relationship between sterile single-use catheters or clean reused catheters and the incidence of urinary tract infections (UTIs). After investigation of the 13 trials that met the inclusion criteria, it was stated that there were no definitive studies that illustrated the incidence of UTIs is affected by sterile single-use or coated catheters compared to clean reused catheters. This systematic review concluded that based on the current data, it was not possible to state that one catheter method is better than another and further research on the topic was strongly recommended (28).

Håkansson performed a narrative review in 2014 to summarize all relevant parts needed to make an informed decision whether to choose for single use of reusable catheters in CIC. All relevant found publications were screened and an overall conclusion was formed. The main conclusion of this narrative review was once again that further clinical research is needed to verify/reject safety differences between reuse/single-use catheters (12).

Conclusion of the available literature:

There are no randomized trials available in literature that compare single use and reusable catheters in patients who CIC. Furthermore, the available systematic reviews present conflicting conclusions on the basis of the same studies. Most articles note this lack of knowledge.

#### **6.4 Summary of known and potential risks and benefits**

The possible disadvantages of reusable catheters are increased risk of UTIs, effectiveness of cleaning method, damage to the urethra and increased patient burden because of the extra time spend on cleaning the catheter. The possible advantages or benefits of reusable catheters include more patient choice, cost saving, reducing fear of running out of catheters, and environmental advantages.

#### **6.5 Description and justification of route of administration and dosage**

All patients will CIC 4-6 times a day, depending on their needs, this will not differ between the intervention and the control group. Patients in the intervention group will use the

reusable catheter and the control group will remain using the single use catheter. All patients are able to catheterize themselves through the urethra.

The reusable catheters are fabricated by Create Medic, a Japanese medical manufacturer with a broad experience in urological products. The reusable catheters are made by the CE-marked manufacturer and registered in the Z-index, so it will be reimbursed through the Dutch health insurances. An independent retailer will provide the catheters to the suppliers in the Netherlands. When a patient decides to withdraw from this trial, they can return the given catheters to the supplier.

#### **6.6 Dosages, dosage modifications and method of administration**

Not applicable.

#### **6.7 Preparation and labelling of Investigational Medicinal Product**

Not applicable.

#### **6.8 Drug accountability**

Not applicable.

## **7. NON-INVESTIGATIONAL PRODUCT**

### **7.1 Name and description of non-investigational product(s)**

Not applicable

### **7.2 Summary of findings from non-clinical studies**

Not applicable

